### Monitoring

For the strategies to be viable outside the trial, first-line cure rates need to be high (>90%). The design of the trial therefore allows for failing groups to be stopped early at any time and subsequent patients to be randomly assigned to more successful groups. Individual performance of groups receiving shortening strategies will be monitored during recruitment by an independent DMC that will make decisions on whether a group should be stopped. Groups receiving standard 12-week treatment will not be monitored as this is the licensed duration with cure rates of more than 90% [28, 29]. Interim analyses will not be comparative as the aim of monitoring is not to find the best strategy but to find any strategy that meets a minimum acceptable cure rate that may also be non-inferior to standard treatment as different strategies may benefit different patient populations.

Analyses of cure rates will follow the Bayesian paradigm to allow the probability of the true cure rate being below different thresholds to be calculated: recruitment into a group will stop if there is a greater than 0.95 posterior probability of the true cure rate being less than 90% (Pr(true cure rate <0.9|x) >0.95, where x is the data currently observed). The primary monitoring is combined across genotypes; if the combined group reaches the stopping guideline, each genotype stratum will be tested separately and the DMC will have the discretion to stop only those strata reaching the stopping criteria. Differences in stopping groups across strata are likely to occur only when there are extreme differences in the cure rates between the strata, which is not expected, and so the operating characteristics of the trial are based on stopping combined strata only. If neither stratum reaches the stopping criteria despite the combined strata doing so, it will be at the discretion of the DMC whether to stop recruitment into the stratum or group.

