At interim analyses, there is greater uncertainty about the performance of the shortening strategies. Therefore, when the prior was determined, it was assumed that one strategy would fail completely such that all four groups receiving that strategy, of a total of 12 tested, would meet the stopping guideline. As each individual outcome is assumed to be Bernoulli-distributed and therefore distribution of all outcomes is binomial, a beta prior was chosen as this is the conjugate prior for the binomial distribution. The mean of the prior was fixed at 0.9, and the effective sample size of the prior was varied until a distribution was found such that there was a roughly 0.33 probability of a cure rate of less than 90%; roughly 0.33 probability was chosen as 4 out of 12 randomly assigned groups are expected to fail and therefore have a true cure rate of less than 90%. The prior chosen was beta (4.5, 0.5) with mean 0.9, variance 0.015 and a 0.34 probability of a cure rate of less than 90%. The relatively low precision of the prior will allow greater influence of the data in the posterior distribution. If the stopping guideline is met, sensitivity analyses using priors informed by observed cure rates in other randomly assigned groups or strata will be performed and will be provided to the DMC to help inform their decision to stop a group.

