## Results and Discussion

### Characteristics of Bayesian stopping guideline for individual groups

The minimum number of failures required to satisfy the stopping criteria for the main monitoring beta (4.5, 0.5) prior and for each number of analysed patients is listed in Table 3. The probability of stopping a group is then the probability of observing the required number of failures in the group. When the true cure rate is 90%, the probability of incorrectly stopping a group is always less than 0.05 and this decreases as the true cure rate increases. It is expected from the specification of the stopping guideline that when the true cure rate is equal to the mean of the prior, the probability of stopping a group is 0.05, so the probability of incorrectly stopping a group is always maintained below the correct level. The calculated probability is not exactly 0.05 and differs depending on the number of patients analysed due to the discrete nature of the outcome.

**Table 3 Tab3:** Number of failures needed to stop a drug strategy group for each number of analysed patients

Analysed patients	Minimum number of observed failures needed to stop group^a^	Maximum probability of stopping group if true cure rate equals:		Minimum probability of stopping group if true cure rate equals:			
		90%	95%	90%	80%	70%	60%
3–7	3	0.026	0.004	0.001	0.008	0.027	0.064
8–13	4	0.034	0.003	0.005	0.056	0.194	0.406
14–20	5	0.043	0.003	0.009	0.130	0.416	0.721
21–26	6	0.040	0.002	0.014	0.231	0.637	0.904
27–33	7	0.042	0.001	0.015	0.287	0.744	0.958
34–39^b^	8	0.037	0.001	0.017	0.367	0.844	0.986
40–41^b^	8	0.048	0.001	0.042	0.563	0.945	0.998
42–48	9	0.046	0.001	0.021	0.469	0.920	0.997
49–55	10	0.044	0.0004	0.022	0.528	0.952	0.999
56–63	11	0.047	0.0003	0.021	0.580	0.971	1.000
64–71	12	0.048	0.0002	0.023	0.648	0.985	1.000
72–78	13	0.045	0.0001	0.025	0.705	0.993	1.000

Groups will recruit a minimum of 78 patients with 39 patients in each stratum if recruitment is not stopped into that group. If recruitment is stopped into one group, the maximum number of patients in each other group and the other stratum for that group will be higher

Maximum and minimum probabilities are for the range of analysed patients

^a^ More than 0.95 posterior probability of the true cure rate being less than 90% (Pr(true cure rate < 0.9|x) > 0.95, where x is the data currently observed, with the beta (4.5, 0.5) prior which has mean = 0.9 and variance = 0.015

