The overall probability of stopping a group, and therefore making a correct decision or incorrect decision to stop recruitment into a group (again analogous to the frequentist concepts of power and type I error), shows results similar to those given above (Supplementary Table 1, Additional file 1). For cure rates of more than 90%, the probability of incorrectly stopping a group is always maintained less than 0.05, and for cure rates of less than 90%, there is a high probability of correctly stopping a group, and almost all groups are stopped when the true cure rate is not more than 70%. The probability of incorrectly not stopping groups with cure rates of about 80% is 12%, and for cure rates of 90%, a group is far more likely not to be stopped than correctly stopped. However, as described above, for our design this is not as much of a concern as it may be for other trial designs because the aim of the monitoring is to stop clearly inferior regimens rather than those close to the arbitrary 90% threshold.

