### Limitations of the design

A potential weakness in the design is that the sample size was not originally calculated using Bayesian principles, but primary analyses will be conducted using Bayesian methods to allow for the calculation of posterior probabilities exploring the difference in cure rates between the interventions. However, for the non-inferiority comparisons, sample size estimates obtained using Bayesian methods are similar to or smaller than those obtained using frequentist methods [34], suggesting that our design is likely to be conservative. Additionally, secondary analyses will use frequentist methods for comparison. For interim analyses, the probability of correctly stopping a group, analogous to the frequentist concept of power, is determined by the true cure rate in the group and the number of analysed patients at each analysis and not by the overall group size.

The timing of and the number of patients at interim analyses are determined by at least one group, usually the 4-week treatment group with PEG-IFN since this has the shortest overall treatment duration, reaching a certain probability threshold of being stopped. This may mean delays in identifying unsuccessful groups receiving other strategies. This is unlikely if groups have cure rates lower than the average cure rate because, as discussed above, these will be detected faster than anticipated, but delays may occur if the cure rate is above the average but less than 90%. As the treatment length of patients in the RGT groups is unknown until after their day 7 visit, it is not possible to stagger treatment start dates so that the length between randomisation and EOT is the same for all strategies. Staggered treatment start might also lead to dropout after randomisation but before starting treatment, leading to inefficiency and potential bias. During the trial, cure rates will be monitored in all groups. If the cure rates are not as anticipated, either they are higher and lower than expected, and so our derived schedule is inappropriate based on these cure rates then the timing can be adjusted wih no penalty to the probability of incorrectly stopping recruitment into a randomised group, due to the use of Bayesian monitoring [22].

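### Changing the interim schedule does change the probability of wrongly stopping a group: at 90% cure it runs from about 4–5% with the four planned looks to about 9–10% with monthly looks to month 24

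*Protocol article*

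**What the plan says.** - **Limitations of the design:** if cure rates are not as anticipated, the interim timing may be changed with "no penalty to the probability of incorrectly stopping recruitment into a randomised group, due to the use of Bayesian monitoring".
- **Characteristics of Bayesian stopping guideline for individual groups:** "When the true cure rate is 90%, the probability of incorrectly stopping a group is always less than 0.05". This is supported by Table 3, which treats each number of analysed patients as one look. The section explains the figure by an argument that opens "It is expected from the specification of the stopping guideline that when the true cure rate is equal to the mean of the prior" and arrives at 0.05. It then turns to the overall probability of stopping, calls correct and incorrect decisions "again analogous to the frequentist concepts of power and type I error", and says that the overall probability of incorrect stopping stays below 0.05 for cure rates above 90%.
- **Monitoring:** "The design of the trial therefore allows for failing groups to be stopped early at any time". The guideline is met when the posterior probability of a cure rate below 90% exceeds 0.95, under a beta(4.5, 0.5) prior.
- **Timing of interim analyses:** four looks are planned, at months 7, 10, 13 and 18. Monthly looks are set aside because of the resources they would need; their effect on false stopping is not mentioned.

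**The concern.** Two quantities are run together. One is the posterior probability that a group's cure rate is below 90%, given its data. Its meaning does not depend on how often the data were examined. The other is the probability, at a fixed true cure rate, that a group ever meets the guideline. That is a repeated-sampling property of boundary and schedule together. The sentence in the limitations section names the second and claims for it the immunity that belongs to the first.

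The supporting argument, that a 0.95 cut-off implies a 0.05 stopping probability when the truth equals the prior mean, is not a general result. It holds approximately at a single look, as Table 3 shows, and does not carry over to several.

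A DMC relying on the sentence would take extra or moved looks to be free. The article itself considers it more important to keep groups above 90% than to stop groups slightly below, so the error affected is the one the design most wants to limit. Recruitment lost to a wrongly closed group goes to other groups, since later patients are assigned to those still open.

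**Working it through.** **Inputs.** Guideline and beta(4.5, 0.5) prior: Monitoring. Outcome model: "each individual outcome is assumed to be Bernoulli-distributed and therefore distribution of all outcomes is binomial" (Monitoring). Patients analysed per group at the four looks (Table 4): PEG-IFN 5, 14, 24, 42; RGT 3, 11, 21, 39; induction/maintenance 2, 8, 17, 35.

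**Step 1: boundary.** With n patients analysed, the boundary is the smallest number of failures f for which BetaCDF(0.9; 4.5 + n − f, 0.5 + f) > 0.95.

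**Step 2: reproduce Table 3.** The single-look probability is P(X ≥ f), with X binomial(n, 0.10). All Table 3 boundaries and probabilities reproduce to within 0.001. The 90% column maxima, for example, come out as 0.026, 0.034, 0.043, 0.040, 0.042, 0.037, 0.048, 0.046, 0.044, 0.047, 0.048, 0.045.

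**Step 3: several looks.** Exact recursion: carry forward the distribution of failures among paths not yet stopped, add the binomial failures of newly analysed patients, remove paths at or beyond the boundary, and sum what was removed.

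PEG-IFN at 90% cure, boundaries 3, 5, 6, 9 at n = 5, 14, 24, 42:

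0.0086 + 0.0071 + 0.0200 + 0.0105 ≈ 0.046.

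**Step 4: move one look.** At n = 41, eight failures give a posterior of 0.9500 (just above the cut-off). At n = 42, eight give 0.944 and nine are needed. With looks at 5, 14, 24, 41:

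0.0086 + 0.0071 + 0.0200 + 0.0294 = 0.065.

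Shifting all four looks of a strategy together by −2 to +7 patients gives values from 4.4% to 8.2% across the three strategies.

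**Step 5: add looks.** Monthly counts per group are not in the article. I interpolated between the Table 4 counts and added 52/14 × 0.95 ≈ 3.5 patients per group per month after month 18. For PEG-IFN this gives 5, 8, 11, 14, 17, 21, 24, 28, 31, 35, 38, 42 to month 18, then 46, 49, 53, 56, 60, 63.

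Probability of stopping at 90% cure:

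| Schedule | PEG-IFN | RGT | Induction/maintenance |
|---|---|---|---|
| Four planned looks | 4.6% | 5.3% | 4.4% |
| Monthly, months 7–18 | 6.8% | 7.8% | 6.8% |
| Monthly, months 7–24 | 9.6% | 9.7% | 9.3% |
| Every outcome to n = 78 | 14.2% | 14.2% | 14.2% |

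Deriving monthly counts instead from the Fig. 2 recruitment totals, with 16-, 20- and 24-week lags to EOT + 12 and looks from month 5 to 24, gives 11.0–11.8%.

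**Step 6: true cure rates above 90%** (range over the three strategies):

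| True cure rate | Four looks | Monthly to month 24 |
|---|---|---|
| 91% | 2.9–3.3% | 6.0–6.3% |
| 91.7% | 2.1–2.3% | 4.1–4.5% |
| 95% | 0.2–0.4% | 0.4–0.7% |

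**Step 7: does every added look matter?** No. Adding n = 3, 4, 21, 22 or 23 to the PEG-IFN schedule changes nothing, because a planned look with the same failure boundary follows. One extra look placed before the fourth takes the figure to at most 6.5% (PEG-IFN, n = 41), 6.9% (RGT, n = 20) or 6.0% (induction/maintenance, n = 33).

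**The case against.** **The plan allows retiming, not more looks.** The sentence speaks of adjusting timing. Timing of interim analyses keeps patient numbers similar when recruitment is delayed, calls monthly looks impractical, and Alternative designs rejects analysis after every outcome. This stands in part: nothing shows that monthly looks are intended, and one extra look adds at most about 2 percentage points. But Step 4 shows that moving a look without adding one is enough to change the probability.

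**The effect sits at an arbitrary boundary.** This stands. The article calls the 90% target largely arbitrary. Table 5 puts shortened-treatment groups at 91.7% or higher, where even monthly looks to month 24 stay below 5%. The guideline also leaves the decision to the DMC, with prior-sensitivity analyses to hand.

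**Bayesian monitoring does protect something.** It does. Averaged over the beta(4.5, 0.5) prior, the chance that a stopped group truly cures at least 90% is 1.4% with four looks and 2.2% with monthly looks (PEG-IFN counts), both under the 5% implied by the cut-off. That is not the probability the sentence names.

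**Stronger readings.** A reader might infer that every added look raises the risk, that the four-look plan is unsound, or that a bound on falsely stopping any of the 12 groups is breached. The first is untrue (Step 7). On the second, the four planned looks give roughly the stated control, with RGT only slightly above 0.05 at exactly 90%. On the third, the article claims no control across groups.

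**Conclusion.** The no-penalty statement is wrong under the article's own definition of incorrect stopping. An added look can never lower that probability and usually raises it; moving a look can shift it either way. At 90% cure the per-group figure is 4.4–5.3% for the planned schedule and about doubles, to 9–10%, with monthly looks to the end of recruitment.

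The planned-look and every-outcome figures are exact given the prior, the cut-off and binomial outcomes. The monthly figures also rest on interpolated counts. The 41-versus-42 comparison takes Table 4's count at face value; the 0.710 average stopping probability printed there for the fourth PEG-IFN look does not reproduce (0.635 at 42, 0.696 at 41), so the exact count behind it is uncertain.

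The four-look design stands. What needs correcting is the stated freedom to depart from it at no cost, and the practical harm is limited to groups whose true cure rate is close to 90%.

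**What to change.** 1. In Limitations of the design, replace the no-penalty sentence: the posterior keeps its meaning under a changed schedule, but the cumulative probability of incorrectly stopping a group at a fixed cure rate does not stay the same.
2. In the section on the stopping guideline's characteristics, say that the below-0.05 statement and Table 3 apply to a single look, and limit the prior-mean argument accordingly.
3. Before any revised schedule is adopted, recompute the cumulative probability of stopping at 90% and at 80% cure for each strategy, and give both to the DMC.

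The cost is two reworded sentences and a short exact calculation per schedule change.

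Raising the posterior cut-off when looks are added is an option with a price, and need not be prescribed. With monthly looks to month 18 and a cut-off of 0.98, false stopping at 90% falls to about 3%, but only 37–45% of groups with 80% cure are stopped, against 46–56% with the four planned looks at 0.95.

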### Sample size

The sample size of the trial was derived on the basis of the null hypothesis that the true cure rate was 90% in each group compared with an alternative, unacceptably low, cure rate of 70%; assessment of power at the final analysis given this sample size is discussed later. For a single stratum within a single randomly assigned group, given 90% power and one-sided alpha of 0.05, and 5% loss to follow-up by EOT + 12, 39 patients would be required per group to exclude the cure rate being lower than 70% based on a single-group test. There are 14 groups and two genotype strata, giving a total sample size of 1092 patients (39*14*2). For final comparisons at trial closure, the null hypothesis is that all groups will achieve the more than 90% cure target and be included in the final analysis. There will then be 546 per group for the regimen comparison (non-inferiority; comparing the two WHO-recommended drug regimens against each other), 156 in the control group and 312 per intervention group for the strategy comparison (non-inferiority; comparing each of the three treatment-shortening strategies versus the licensed 12-week control duration), and 468 per group for the ribavirin comparison (superiority; comparing each treatment-shortening strategy with and without ribavirin). The total sample size is fixed at 1092 patients; if individual groups are stopped early, any subsequent patients will be randomly assigned to open groups where possible (depending on the delay between randomisation, identification of primary endpoints and interim analyses), so numbers in each fully recruited group may be higher. This is appropriate in a pragmatic trial, where the goal is to maximise information gained about many different strategic approaches to treatment rather than to minimise sample size per se.

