The choice of the non-inferiority margin was based on clinical judgement and the size of margins used in other trials of anti-infectives with relatively low failure rates such as community-acquired pneumonia [30]. In particular, a smaller 5% margin is chosen for the drug comparisons because in practice they are likely to have similar advantages and disadvantages. In contrast, the different drug-sparing strategies have a variety of different advantages and disadvantages (in terms of additional visits vs. less drug vs. different drugs vs. weekends off; Table 1) which could be differentially balanced against overall cure rates, particularly considering impact on health-care provision (e.g., through directly supervised therapy). Thus, a greater non-inferiority margin (here 10%) is relevant to drug-shortening because the potential benefit in terms of numbers treated for the same fixed budget is much greater. Regulatory guidance recommends that non-inferiority margins be chosen to ensure that the difference between an intervention and the active control (here 12 weeks’ duration) would not exceed that between the active control group and a hypothetical placebo (or other standard control group, here the previous standard of care of 12–48 weeks of PEG-IFN) [30]. As cure rates with 12–48 weeks of PEG-IFN were about 70% in genotype 6 [31], with similar or lower cure rates in other genotypes, and as we expect more than 90% SVR12 in all groups, our non-inferiority margins of both 5% for the regimen comparison and 10% for the strategy comparison would ensure this.

From initial power calculations based on all 14 randomly assigned groups, assuming that the overall cure rate is 95%, the fixed total sample size of 1092 patients above provides 97% power to demonstrate non-inferiority between drug regimens based on a 5% margin and 96% power to demonstrate non-inferiority between shortening strategies based on a 10% margin, both with one-sided alpha of 0.05. For superiority comparisons (conducted for ribavirin and any comparison that meets non-inferiority above) and two-sided alpha of 0.05, these numbers provide more than 90% power to detect absolute differences in SVR12 of 5% for regimen or ribavirin comparisons and more than 80% power to detect absolute differences in SVR12 of 7% or more for the strategy comparisons.

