### Statistical analysis

The final analysis will estimate risk differences between groups using marginal effects after logistic regression. The model will include all main randomised effects and strata and will test interactions between all randomisations (Supplementary Methods, Additional file 1). Interactions will be included in the final model only if the 95% credible interval for the interaction term excludes no effect (*P* <0.05 for frequentist analyses). The interaction between regimen and strategy will include all levels of strategy. Owing to the partial factorial randomisation, the interaction between ribavirin and strategy will not include the standard treatment length strategy. Comparisons of regimens and of strategies will be non-inferiority analyses, and the ribavirin comparison will be a superiority analysis. Primary analysis will be intention-to-treat using Bayesian methods and 90% credible intervals. Secondary analyses will consider per-protocol populations, frequentist methods, and 95% credible and confidence intervals.

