The power calculations for the final analysis assume that all groups will be included and that no groups have been stopped. It is possible that power will be lower if fewer groups are included, but for most comparisons with a full sample, power is very high and is likely to remain acceptable at the final analysis even with the exclusion of some patients. To help preserve power, if groups are stopped early subsequent patients will be randomly assigned to open groups. The power calculations were also estimated by using frequentist methods, although the primary analysis will use Bayesian methods. However, as power is extremely high, the analogous concept to power in Bayesian analysis, that for non-inferiority comparisons the lower credible interval bound is above the non-inferiority margin, is likely to be similarly high. Additionally, owing to the many possible combinations of strata and groups that could be stopped with different true and observed failure rates and at different times, examining the impact of stopping multiple combinations would require a large number of assumptions, probably also using a factorial simulation design, and hence would be a large piece of additional work in its own right. This is also the case for examining the impact of stopping multiple randomly assigned groups on other aspects of the trial, such as bias.

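### Two sections imply that groups stopped at interim are left out of the final analysis, which conflicts with the intention-to-treat rule and, if followed, would raise the false non-inferiority rate for shortening strategies above 5%

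*Protocol article*

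**What the plan says.** All references are to the protocol article.

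- **Monitoring.** The rule acts on enrolment: "recruitment into a group will stop if there is a greater than 0.95 posterior probability of the true cure rate being less than 90" per cent. It applies to each shortening group separately. The standard 12-week groups are not monitored.
- **Sample size.** For the final comparisons, "the null hypothesis is that all groups will achieve the more than 90% cure target and be included in the final analysis". The comparison sizes follow from that, including "156 in the control group and 312 per intervention group for the strategy comparison". The total stays at 1092, and patients who would have entered a stopped group go to open groups.
- **Statistical analysis.** "Primary analysis will be intention-to-treat using Bayesian methods and 90% credible intervals".
- **Limitations of the design.** Power might fall if fewer groups are included, but "power is very high and is likely to remain acceptable at the final analysis even with the exclusion of some patients". The section adds that the effect of stopping several groups on bias was not examined.

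No section says whether patients already randomised to a stopped group stay in the final model.

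**The concern.** If stopped groups stayed in the model, stopping would leave neither fewer groups nor excluded patients, because the total is fixed and later patients are reassigned. The natural reading of the Sample size and Limitations wording is therefore that stopped groups drop out. That cannot be squared with intention-to-treat.

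The stopping rule is driven by the primary endpoint. Leaving out stopped groups keeps those whose failures happened to be few, so a strategy's pooled cure rate is biased upwards. Control is never subject to this selection, so in the strategy comparison the bias runs one way, towards non-inferiority. A Bayesian analysis does not remove the problem: disregarding the stopping rule is defensible only when all the data that drove it stay in. The article treats exclusion purely as a question of power, so an analyst following that wording would have no warning about error rates.

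**Working it through.** **Inputs.**
- Stopping rule: posterior probability above 0.95 that the cure rate is below 90% (Monitoring). "The prior chosen was beta (4.5, 0.5) with mean 0.9, variance 0.015".
- Patients with outcomes per group at the four interim analyses (Table 4): PEG-IFN 5/14/24/42, response-guided 3/11/21/39, induction/maintenance 2/8/17/35.
- Randomised per group at those times: 205, 361, 517 and 777 divided by 14, or about 15, 26, 37 and 56.
- Final sizes: four groups of 78 (312) per strategy against 156 controls.
- Margin 10 points; non-inferiority power is stated "both with one-sided alpha of 0.05", which matches a 90% interval.
- Control cure rate is not fixed, so a range is used: 93.3%, 95% and 96.7% from Table 5, and 90% as the floor of the article's expectation of more than 90%.

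**Step 1: reproduce the stopping rule.** With f failures in n patients the posterior is beta(4.5 + n − f, 0.5 + f).
- n = 39, f = 8: beta(35.5, 8.5) gives Pr(cure < 0.9) = 0.961, so stop; f = 7 gives 0.909, so continue. The chance of 8 or more failures at a true 90% is 0.037.
- n = 78, f = 13: beta(69.5, 13.5) gives 0.954; the chance at a true 90% is 0.045.

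All Table 3 thresholds and its maximum probabilities at 90% reproduce. Ten of the twelve average stopping probabilities in Table 4 reproduce to three decimals. The others are induction/maintenance at n = 8 (0.146 against 0.150) and PEG-IFN at n = 42 (0.635 against 0.710). The 0.710 is what 8 failures at n = 42 would give; Table 3 requires 9, and 9 is used here.

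**Step 2: simulate a strategy at the margin.** All four groups have a true cure rate of control minus 10 points. Each stops automatically when it meets the rule. Non-inferiority is claimed if

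q − c − 1.645 × √[c(1 − c)/n_c + q(1 − q)/n] > −0.10,

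with q and c the observed strategy and control cure rates, and n and n_c the corresponding numbers analysed. If all four groups stop and are excluded, no claim is made. There were 100,000 runs per scenario; ranges are across the three strategies.

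| Control / strategy | Stopped groups kept | Stopped groups excluded |
|---|---|---|
| 96.7% / 86.7% | 4.5-4.7% | 7.0-8.0% |
| 95% / 85% | 4.3-4.5% | 8.0-9.6% |
| 93.3% / 83.3% | 4.2-4.4% | 9.1-11.3% |
| 90% / 80% | 4.2-4.4% | 11.6-14.1% |

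At 95% / 85% each group has about a 20-25% chance of stopping, and some but not all of a strategy's groups stop in 58-69% of trials. Exclusion lifts the strategy's cure rate by 0.9 to 1.2 points on average. At 90% / 80% the lift is 2.1 to 2.8 points.

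**Step 3: vary the method.**
- Main-effects logistic model with marginal risk differences (6,000 runs): excluded 7.2-7.7%, 8.0-10.0% and 11.2-14.3% at control 96.7%, 95% and 90%; kept 4.2-5.0%.
- Freed patients spread over all open groups: 7.1-8.0%, 8.0-9.3%, 8.9-11.0% and 11.6-13.5% at control 96.7%, 95%, 93.3% and 90%.
- All freed patients sent to the same strategy's open groups (an extreme case): about 7.5-11% for control 90-95%.

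Every group sits at the margin in these scenarios, so the surviving groups are inferior too. The excess is type I error and not a change of estimand.

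**Step 4: regimen comparison.** With one regimen exactly 5 points worse in all groups (95 v 90%, 92 v 87%, 90 v 85%), exclusion gives 6.3-8.0% against about 5% when all are kept.

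**The case against.** A reader might infer that the plan directs stopped groups to be dropped, and that its error rate is therefore 8-14%. The documents do not support that. The Sample size sentence is a planning assumption used to derive group sizes. The Limitations remark is hedged and concerns power. The explicit analysis rule is intention-to-treat, and monitoring closes recruitment only. The Alternative designs section adds that monitoring is not meant to require a given cure rate within a group at the end of the trial. Model details are referred to supplementary methods that are not shown, and the article openly says that bias from stopping was not studied.

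The size is also conditional:
- The upper end needs control at 90%, whereas the analysis prior has mean 95% and Table 5 spans 93.3-96.7%.
- All four groups must sit at the margin.
- Stopping is simulated as automatic, while the article leaves the decision to the data monitoring committee, with discretion over genotype strata.
- The beta(4.75, 0.25) control prior was not modelled.
- The one-way argument does not carry over to regimens, because both regimens contain monitored groups.

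These points limit the size and rule out saying that the plan mandates exclusion. They do not remove the contradiction. This is not a detail merely left to another document: the article speaks to it in several places, and they disagree. If the intention-to-treat rule governs, the wording in the other two sections is wrong and could mislead whoever implements the analysis.

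**Conclusion.** The point stands as an internal conflict over the primary analysis set, with exclusion implied and not prescribed. If the implied exclusion were followed, a strategy exactly at the 10-point margin would be declared non-inferior in about 7-10% of trials at control cure rates of 95-96.7%, about 9-11% at 93.3%, and up to about 14% only at 90%. Keeping everyone holds the rate at or just under the nominal 5%. These figures assume four equal groups at the margin, automatic stopping at the projected interim counts, no loss to follow-up, and a frequentist stand-in for the Bayesian analysis with flat effect priors. The regimen comparison is affected less, and through a different mechanism: the worse regimen's groups stop more often than the better regimen's.

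**What to change.** 1. In Sample size, Statistical analysis and Limitations, state that the primary analysis of all three comparisons (regimen, strategy, ribavirin) includes every randomised patient in the assigned group, including patients in groups or genotype strata later stopped.
2. Remove the wording that makes inclusion depend on meeting the cure target, and reword the Limitations remark so that stopping means smaller groups, not excluded ones.
3. Report any analysis without stopped groups only as a labelled sensitivity analysis, with a note that it selects on the outcome.

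The cost is wording only. No patients are added and no interim rule changes; the primary analysis keeps more patients, and the non-inferiority error rate stays near its design value. What is given up is the more favourable look of a strategy whose poor groups have been removed. The text should be settled before interim results could influence the choice.
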